## Abstract

**Background:**

The obesity rate among women in Côte d'Ivoire is rising, particularly in urban areas. Merchantry is the leading occupation for women in the country, and merchant women face a high risk of obesity owing to their sedentary lifestyle. A previous survey indicated that the obesity rate among merchant women was 30%, double the national average. Furthermore, 82.2% of merchant women with obesity were unaware of their condition, and 40.1% expressed no interest in losing weight. While most weight loss programs target individuals ready to lose weight, community interventions should also address those with minimal readiness. Additionally, low-cost weight-loss interventions that do not require health professionals are needed in countries with limited medical resources. Smartphones could offer a cost-effective solution as they enable self-monitoring and remote communication.

**Objective:**

This study will evaluate a low-cost smartphone-based intervention that targets individuals who are not ready to lose weight without the involvement of health professionals.

**Methods:**

The intervention will run for 6 months, and its efficacy will be assessed in an unblinded, parallel-group, randomized controlled trial with 108 participants per group. All direct interventions for participants in this study will be carried out by staff without medical qualifications. The intervention group will receive weighing scales and be encouraged to record their weight with a smartphone app. Health education will be provided via weekly group messages and monthly phone calls. The evaluation will be conducted face-to-face. The primary outcome will be the weight change, and the secondary outcome will be differences in body fat percentage, abdominal circumference, and stage of behavioral change in weight loss behaviors from baseline to 3, 6, and 12 months.

**Results:**

In accordance with this protocol, the recruitment of participants started on August 26, 2024. A total of 216 participants were allocated, with 108 in the intervention group and 108 in the control group. The baseline survey began on November 15, 2024, and is currently ongoing as of the end of November 2024.

**Conclusions:**

This study will be the first in sub-Saharan African countries to implement a smartphone app-based weight loss program in sub-Saharan Africa that does not require direct intervention by health care professionals but specifically targets communities. Furthermore, if the effectiveness of this program is confirmed, it has the potential to serve as a low-cost sustainable weight loss model at the policy level.

**International Registered Report Identifier (IRRID):**

DERR1-10.2196/69264

## Introduction

### Background

Obesity caused an estimated 5 million deaths associated with noncommunicable diseases (NCDs) such as cardiovascular diseases, diabetes, cancers, and chronic respiratory diseases [1]. Additionally, its high prevalence in people 18 years and older is a critical issue, at 17.9% for women and 13.6% for men in 2022. In Africa, the obesity rate was 17% in women and 6.8% in men in 2022 [2]. This difference is particularly significant, making obesity among women an urgent issue. The percentage of women with obesity in Côte d'Ivoire has doubled compared to 20 years ago (7.3% in 2002 and 15.7% in 2022) [2].

The characteristics of the occupational style of African market traders indicate that these traders are at high risk of obesity due to long sedentary hours and easy access to food [3-5]. In Abidjan, the largest city in Côte d'Ivoire, 64.3% of working women are merchants [6], and merchant is a common occupation among women from lower- and middle-income groups. A survey of medical facilities in Abidjan also showed that merchantry was the most common occupation among patients with overweight and obesity [7]. Furthermore, our all-inclusive market survey showed that the obesity rate among merchant women is 30% [8], double the national average of 15.3%. This indicates an urgent need to address obesity among individuals in the merchant community.

Obesity is a substantial cause of NCDs such as heart disease and type 2 diabetes [9,10], and weight loss can reduce the risk of NCDs. However, in Côte d'Ivoire, there is no community-targeted weight loss program. In general, weight loss programs often target those who wish to lose weight. However, in African countries such as Côte d'Ivoire, where being plump is a symbol of wealth and power, many individuals with obesity have no desire to lose weight. Notably, 82.2% of merchant women with obesity who work at the targeted market were unaware that they had obesity, and 40.1% did not wish to lose weight (38.6% wished to maintain their current weight and 1.5% wished to gain weight) [8]. Thus, in an environment such as that in Côte d'Ivoire, developing measures to address obesity in communities that include those with minimal readiness for weight loss is necessary.

To increase the willingness of individuals with obesity to undergo weight loss, we must educate them on their condition and reasons to lose weight. Weighing is key to this; however, in our study, 53.3% of merchant women with obesity did not weigh themselves once a year, and 95.5% of them did not own a scale. Regular weighing is effective for weight loss even without interventions such as weight loss programs [11] and is one of the most cost-effective and easiest weight loss methods to implement. In this study, we aim to increase the awareness of one’s own weight through regular weighing, promote awareness of health risks, and increase readiness for weight loss.

Noninvasive exercise and diet are the cornerstones of behavioral therapy as a treatment method for obesity [12]; overweight and obesity management guidelines [13] that include behavior change programs have been established in the United States. However, these are primarily conducted by primary care physicians in medical institutions and require advanced medical personnel and resources such as frequent counseling and elaborate individualized behavioral strategy planning. Therefore, implementing these behavior change programs as is in resource-limited countries such as Côte d'Ivoire is challenging [14,15].

Mobile health is cost-effective and impactful in supporting diet and exercise regimens [16-20]. Self-monitoring using smartphones is more effective than other methods of weight management [20]. Enhanced social support through online social networking services (SNSs) can also be effective. For example, Facebook groups have shown weight loss benefits [21]. In Côte d'Ivoire, WhatsApp is a popular private communication tool; however, studies on implementing behavior change using WhatsApp are limited [22]. Most studies that use smartphone apps and SNSs have been conducted in high-income countries. Such studies are limited in sub-Saharan Africa because sociocultural backgrounds and the use of smartphones and SNSs are different.

The prevalence of smartphones in sub-Saharan Africa was 45% in 2019 and is expected to steadily increase [23]. In our previous study, 77% of female traders in the target markets used smartphones [8], suggesting that interventions using smartphones are feasible. Smartphone use is important in areas requiring low-cost interventions.

Community-based weight loss interventions in sub-Saharan Africa include a group session intervention in South Africa [24] and a program initiated in Burkina Faso that includes multiple in-person dietary counseling sessions with experts [25]. These include multiple in-person sessions with health professionals, counseling, and health education.

Considering their feasibility in areas where medical resources are scarce, smartphone use that allows for remote intervention and methods that require less intervention by health care workers are required.

In this study, we aim to examine the effectiveness of a low-cost versatile weight loss intervention that can be implemented without intervention by health professionals in a community that comprises those with minimal readiness for weight loss. Specifically, this study will examine the effectiveness of a weight loss intervention that incorporates weight measurement promotion, the use of a smartphone app, and communication with non–health professionals among female merchants with obesity in Côte d'Ivoire. This will be an unblinded, parallel-group, randomized controlled trial.

This paper outlines the study protocol of a randomized controlled trial, describing the intervention and examining its effectiveness.

### Hypothesis

This study hypothesizes that the intervention group will achieve a weight loss of at least 2% [13] from baseline to 6 months, significantly differing from the control group. We will consider 2% weight loss as a clinically meaningful value; since the average weight of women with obesity in the target market is 85.6 kg [8], the equivalent of 2% is –1.7 kg. Based on the results of previous studies [19], this goal was deemed feasible.

## Methods

### Research Design

This study will focus on market A in Abidjan, Côte d'Ivoire. The effectiveness of the weight loss intervention will be tested in a parallel-group (1:1) randomized controlled trial among Merchant women with obesity within this market. As standard treatment, the control group will be weighed and provided with their BMI based on physical measurements, whereas the intervention group will receive a scale and the weight loss intervention using a smartphone app, and the differences will be compared. The study will be unblinded, and the effectiveness of the program will be evaluated after 6 months. In addition, a follow-up evaluation will be conducted 12 months later to assess sustained changes after the intervention is complete. We followed the SPIRIT (Standard Protocol Items: Recommendations for Interventional Trials) 2013 statement and CONSORT-eHEALTH (Consolidated Standards of Reporting Trials of Electronic and Mobile Health Applications and Online Telehealth) checklist (V 1.6.1).

### Eligibility Criteria

The target population will be female merchants between 18 and 65 years of age working in market A with a BMI ≥30 who own a smartphone for personal use and who can use WhatsApp. The exclusion criteria included those who are pregnant or lactating, those who are found pregnant during the intervention period, those for whom weight loss is contraindicated (due to a cancer diagnosis, eating disorders, poorly controlled hypertension, diabetes, etc), and those using physician-prescribed weight loss medication. If they have medical records, we will review them for the eligibility assessment. If they do not, we will ask about their conditions in detail and make a judgment.

### Recruitment

Four interviewers and supporters will visit the target market, approach potential participants, and screen them to see if they satisfy the inclusion criteria by asking a few questions and taking physical measurements (weight and height measurements). If the participants were eligible, we explained the purpose of the study, the intervention and procedures, and the eligibility and exclusion criteria in detail and returned at least half a day later to obtain their signatures on a consent form. We also explained that the participants would be randomly assigned to either the intervention or control group and would not be able to self-select. We explained that all participants would be weighed regularly at the beginning of the intervention as well as 3, 6, and 12 months later, and that their height would be measured at the beginning of the study so that their BMI would be known each time. We further explained that the control group will have access to free scales placed at several locations in market A 12 months after the end of the entire study, which they can use at their leisure. We also informed them that smartphone apps and other devices would be introduced to them at the end of the study.

Participants could withdraw from the study at any time before data collection at 6 months by submitting a consent withdrawal form to a member of the research team.

### Intervention

The weight loss intervention implemented in this study will target communities, including those who have no desire to lose weight, and will be low-cost without direct intervention by health professionals. The basic framework will be based on the American Heart Association (AHA)/American College of Cardiology (ACC)/The Obesity Society (TOS) guidelines for the management of overweight and obesity in adults [13] and the Burkina Faso program [25], which is implemented in the sociocultural context of West Africa. However, since both of these programs include direct intervention by health professionals, which differs from the purpose of this study, the content of the intervention is adapted to the situation in Abidjan in this study (Table 1). The weight loss intervention will be conducted for 6 months. The intervention will be based on self-weighing [11], which has been shown to be beneficial for weight loss, and will include the use of a low-cost personalized support smartphone app [16]. In addition, direct contact with the intervention group will be conducted by Ivorian non–medical professional supporters who were selected based on their research experience within Côte d'Ivoire and have received training for this study.

The intervention consisted of the following three components: (1) promoting weight measurement and encouraging self-monitoring through a smartphone app; (2) health education using a messaging app; and (3) in-person or telephone health education based on the stage of behavior change [26]. Lose it! (FitNow, Inc.) is a weight management app that will be used for weight self-monitoring [27], which has been used in weight loss programs in previous studies [20,28] and is available for free. WhatsApp, which is widely used in Côte d'Ivoire [29], can send and receive images, videos, audio, and text [30], and can deliver a variety of health education messages at low cost [31,32]. In addition, a step-counting app, such as Google Fit (Google Inc) for Android users and Health Care (Apple Inc) for iPhone users, can be installed for weight change and step-count monitoring. These apps will be installed on the smartphones of the intervention group, and participants will receive an orientation on their use. Additionally, they will be able to contact their supporters via WhatsApp to inquire about the use of Lose It! and another app at any time.

Health education should include recommendations for and emphasize the importance of a healthy diet, exercise, and weight measurement. Diet and exercise content should be in line with the “Diet and Exercise” described in the “Obesity” chapter of the Côte d'Ivoire National Disease-Specific Cookbook Guidelines [33]. In-person or telephonic health education will be conducted once a month and tailored to the stages of behavioral change [26] (precontemplation, contemplation, preparation, action, and maintenance) of the target population. Interventions corresponding to the change process [34-36] of each stage are provided. The intervention stimulates interest in weight loss during the precontemplation stage, motivates implementation during the contemplation stage, supports implementation during the preparation stage, supports continuation during the action stage, and supports maintenance during the maintenance stage to maintain confidence in behavior. The intervention and evaluation schedules are shown in Table 2.

To maintain consistency among supporters in the intervention, a manual was developed on how to send health education material via WhatsApp. A manual for telephone interviews was developed, and supporters will conduct telephone interviews according to the manual and provide a report on the content of the interviews. Supporters will be trained on the content of the intervention and the survey to ensure the quality of the intervention and the survey.

No interventions are administered in the control group. For the control group, height and weight are measured at baseline and at data collection at 3, 6, and 12 months, and BMI is calculated and reported on the spot by the supporter. This allows participants in the control group to know their weight and BMI regularly. In addition, after the 12-month survey is completed, scales will be installed in the target markets free of charge so that participants can continue to measure their weights. In addition, we will introduce the app to those who wish to use it.

**Table 1 table1:** Adaptations of the weight loss program following the American Heart Association (AHA)/American College of Cardiology (ACC)/The Obesity Society (TOS) guidelines for the management of overweight and obesity in adults.

Variable	AHA/ACC/TOS guidelines [13]	Intervention adapted to this study	Reason for adaptation
Participants and setting	Individual with obesity who contacted with general practitioner or another medical organization	Community recruitment	Many individuals with obesity are unaware of their obesity risk and do not feel the need to lose weight, making them less likely to visit a health care facility voluntarily.
Intervention method and frequency	In-person, high-intensity (≥14 sessions in 6 months) sessions and counseling for feedback (face-to-face or telephonic)	6 phone calls and 3 face-to-face health education sessions (focused on behavior change stages, not full medical counseling)	For nonmedical interventions, feasibility was considered.
Intervention duration	6 months	6 months	No change
Interventionist	Health professionals (registered dietitians, psychologists, exercise specialists, health counselors, or professionals in training) who adhered to formal protocols in weight management	Trained non–medical professionals over 3 days, covering coaching, intervention methods by behavior change stage, and diet/exercise per Côte d'Ivoire obesity guidelines	Côte d'Ivoire’s limited medical personnel and resources were taken into consideration.
Weight loss goal	Loss of 5%-10% of baseline weight within 6 months	Loss of 2% of baseline weight within 6 months	It is a clinically meaningful minimum value and is feasible according to previous studies [8,19].
Physical activity	Advice by health professionals; increased aerobic physical activity (such as brisk walking) for ≥150 min	Recommend increasing the number of steps in one’s daily routine and establish a step count goal	With limited facilities and resources for fitness programs, the plan recommends daily walking and using a smartphone app for exercise.
Dietary intervention	Advice by health professionals; daily energy deficit of 500 kcal typically achieved with dietary intake of 1200-1500 kcal/d for women	Advice from trained non–health professionals based on the National Recipe Guidelines: offer recommended local dishes and cooking tips	The method is feasible for non–health professionals, using guidelines adapted to local eating habits without calorie calculations, which are difficult for participants and interventionists.

**Table 2 table2:** Enrollment, intervention, and data collection timeline.

			–2 months		–1		0^a^		1		2		3		4		5		6		12
**Enrollment**																					
	Eligibility assessment	✓																			
	Informed consent	✓																			
	Allocation			✓																	
**Intervention**																					
	Distribution of scales					✓		✓													
	App installation and orientation					✓		✓													
	Health education via message app (1 time/wk)							✓		✓		✓		✓		✓		✓			
	In face-to-face health education (at the time of survey)					✓						✓						✓			
	Health education by phone							✓		✓				✓		✓					
**Data collection for intervention group**																					
	Collect data at time of call (weight, stage of behavior change)							✓		✓				✓		✓					
**Data collection for intervention group and control group**																					
	Weight, body fat percentage, and abdominal circumference measurements	✓				✓						✓						✓		✓	
	Height measurement	✓																			
	Structured interview	✓				✓						✓						✓		✓	

^a^The intervention lasted from months 0 to 6.

### Outcome

The primary end point of the study is to compare weight changes from baseline to the end of the intervention (6 months later) between the intervention and control groups.

Secondary end points include the differences in body fat percentage, abdominal circumference, stage of behavioral change in weight loss behaviors such as diet and exercise, percentage of individuals with correct weight perception, degree of body pain (with visual analog scale [VAS]), and self-rated health at the end of the intervention (6 months later) compared to baseline. Simultaneously, the intervention group will be evaluated in terms of the frequency of inputs to the self-monitoring apps, degree of participation in WhatsApp groups, average number of steps taken, and degree of weight loss during the intervention period.

To evaluate the interim process of the intervention, the intervention and control groups will be compared and analyzed in the same manner as described above, 3 months after the start of the intervention. In addition, the intervention group will be evaluated for weight change at 1, 2, 4, and 5 months and for changes in the behavioral change stage of weight loss behaviors such as diet and exercise.

As a follow-up evaluation after the intervention, both groups will be evaluated at 12 months (6 months after the end of the intervention) in the same way.

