### Data Collection Methods

Data will be obtained from supporters visiting the market to conduct face-to-face structured interviews (Multimedia Appendix 1) and anthropometric measurements. Body measurements will be taken at the time of recruitment to measure height and weight, and BMI will be calculated immediately. Subsequent data collection will include weight measurements, body fat percentage, and abdominal circumference. Height will be measured using a hardware SHUREMAN Lock Convex measuring tape (Kenoh Co, Ltd, Japan, model LC-5525) with a locking function, and an InBody (InBody Japan Inc, model H20N) will be used as the body composition scale. Structured interviews will be conducted using a questionnaire asking about sociodemographics, weight perception, behavioral change stages related to weight loss, behaviors related to weight management, body pain level (using the VAS scale), and the use of smartphone apps for weight management.

In addition, the intervention group will be asked about the weight and behavioral change stages of exercise and diet during the monthly telephone intervention.

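### Correct weight perception is counted from a baseline taken after screening disclosure, against controls who get BMI feedback, so it shows only the programme's added effect

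*Protocol article*

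**What the plan says.** **Aim.** The Background section says of regular weighing and its purpose: "we aim to increase the awareness of one’s own weight through regular weighing, promote awareness of health risks, and increase readiness for weight loss". It gives the starting point from a survey of the same market: "82.2% of merchant women with obesity who work at the targeted market were unaware that they had obesity".

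**Endpoint.** The Outcome section lists "percentage of individuals with correct weight perception, degree of body pain (with visual analog scale [VAS]), and self-rated health at the end of the intervention", compared with baseline. Statistical Methods compares the categorical secondary outcomes as plain differences in rates at baseline and at 3, 6 and 12 months.

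**Before the baseline.** Under Recruitment, staff approach women and "screen them to see if they satisfy the inclusion criteria by asking a few questions and taking physical measurements (weight and height measurements". Data Collection Methods adds: "Body measurements will be taken at the time of recruitment to measure height and weight, and BMI will be calculated immediately". For eligible women, "we explained the purpose of the study, the intervention and procedures, and the eligibility and exclusion criteria in detail", and the signature is taken at least half a day later. Eligibility Criteria sets the BMI threshold at 30. Table 2 places eligibility assessment and consent at month -2, allocation at month -1 and the baseline survey at month 0.

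**After the baseline.** For controls at baseline and at 3, 6 and 12 months, the Intervention section says "BMI is calculated and reported on the spot by the supporter". Recruitment tells all participants that their BMI will be known at each weighing. Research Design calls weighing with BMI feedback the control group's standard treatment, while the Intervention section says controls receive no intervention.

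**The concern.** The trial wants to raise awareness in women most of whom did not know they had obesity. Being weighed and learning that a study for BMI 30 or above will take you is itself an awareness step. It comes before the endpoint's baseline and reaches both arms, and BMI feedback then continues in both arms. Three consequences follow for this one endpoint:

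- Change from month 0 leaves out whatever was learned at screening.
- Fewer women remain to be corrected, so there is less room for the arms to separate.
- The control arm is an active comparator for awareness. A small difference could be reported as the programme failing to raise awareness, when it would show only that the programme added little to weighing with BMI feedback. The sentence saying controls receive no intervention invites that misreading.

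A further risk is the order of events within a visit. Weighing and interview fall at the same visits in Table 2, and the text does not fix which comes first. If the perception item follows the feedback, the answer partly records what the woman has just been told.

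**Working it through.** **1. Timing.** Recruitment ran from August 26 to September 8, 2024, and the baseline survey began on November 15, 2024 (Results).
- August 26 to November 15: 81 days.
- September 8 to November 15: 68 days.

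Every woman therefore had at least 68 days between screening and her month-0 answer, in line with Table 2's two months.

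**2. What was disclosed.** Weighing, measuring and explaining "the eligibility and exclusion criteria in detail" are documented for eligible women. The article says BMI was calculated at recruitment; it does not say the value was read out then. A woman who is measured, told she is eligible and told the threshold can infer it, but need not.

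**3. Is there a measure from before disclosure?** Table 2 ticks a structured interview at month -2. Recruitment mentions only a few screening questions, and the survey forms listed as Multimedia Appendix 1 start at baseline. A perception answer from before disclosure is neither shown nor excluded.

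**4. Headroom, as an illustration.** Take the survey figure: 100 - 82.2 = 17.8% aware. Let *s* be the share of unaware women corrected at screening (assumed; not in the documents).
- Month-0 correct perception = 17.8 + 82.2 × *s*
- Largest possible later rise = 82.2 × (1 - *s*)

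| *s* | Month 0 correct (%) | Room left (points) |
|---|---|---|
| 0 | 18 | 82 |
| 0.25 | 38 | 62 |
| 0.50 | 59 | 41 |
| 0.75 | 79 | 21 |

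This also assumes that being unaware in the survey is the complement of correct perception on the trial's item, and that the survey rate applies to consenting smartphone owners. Neither can be checked, as the item is in an appendix not shown.

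**5. Effect on the contrast between arms.** If a share *c* of still-unaware controls and a share *t* of still-unaware programme women are corrected by month 6, the difference is 82.2 × (1 - *s*) × (*t* - *c*). With *c* = 0.2 and *t* = 0.6 (assumed) it is 32.9, 24.7, 16.4 and 8.2 points for the four values of *s*. It shrinks in proportion to 1 - *s* but does not vanish.

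**6. Why no power figure is offered.** With 97 completers per arm (108 × 0.9) and *s* = 0.5, power is about 76% for *c* = 0.2, *t* = 0.6, but about 24% for *c* = 0.2, *t* = 0.4. The result reflects the chosen rates, not anything in the plan.

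**7. Would a month -2 baseline help?** The difference in change between arms is (month-6 programme rate - baseline) - (month-6 control rate - baseline). Screening precedes randomisation, so the baseline term is the same in expectation in both arms and cancels. Moving it from month 0 to month -2 leaves the contrast, and the lost headroom, where they were.

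**The case against.** A reader might infer that the endpoint cannot measure awareness at all. The documents do not support this. Screening disclosure happens before randomisation and is common to both arms, and BMI feedback is the comparator that Research Design declares. The stated aim is awareness through regular weighing, and the home scale, app and education are what separate the arms. The randomised contrast therefore estimates a real and relevant quantity. This part of the objection stands.

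A reader might also extend the point to stage of behavioural change, on the ground that readiness depends on knowing one has obesity. The Background figures speak against that. With 40.1% not wishing to lose weight, 59.9% did wish to, while only 17.8% were aware. If both percentages share a denominator, at least 59.9 - 17.8 = 42.1% wished to lose weight while unaware. The extension is not made here.

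It can fairly be said, too, that question order is a detail for the survey form, that Data Collection Methods names the interview before the measurements, and that the text around the no-intervention sentence already describes the BMI reporting. Naming two activities in a sequence does not fix their order at the visit, though, and the two descriptions of the control arm still differ. These objections reduce the point to a minor one without removing it.

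**Conclusion.** The point holds in a limited form. Month-0 weight perception is recorded after weighing and explanation of the BMI criterion, and controls receive BMI feedback throughout. The endpoint therefore estimates the programme's effect over and above periodic weighing with BMI feedback. It misses any gain made at screening, and its month-0 level is not comparable with the 82.2% survey figure. The loss of headroom is real in direction if screening corrected anyone's perception, but its size is unknown; the 62, 41 and 21 points above rest wholly on assumed correction rates.

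This is minor. It concerns one of several secondary endpoints, and leaves the weight-based primary endpoint and the 108 per group untouched.

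**What to change.** 1. At months 3, 6 and 12, in both arms, ask the weight-perception item before the woman is weighed and told her BMI, and state this order in the protocol.
2. Replace the plain difference in rates for this endpoint with a comparison of the arms at each visit that includes the month-0 perception answer as a covariate. Table 2 puts allocation at month -1 and scale distribution and face-to-face education at month 0, so state whether the month-0 answer was taken before the woman learned her arm and before these steps.
3. Interpret the result as the effect beyond weighing with BMI feedback. Do not set month 0 against the 82.2% figure. Reconcile the no-intervention statement in the Intervention section with the comparator in Research Design.

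The cost is a fixed question order at three visits, a change of analysis wording and a narrower awareness claim. No new visits or staff are needed. A month -2 baseline is not proposed as a remedy, because it would restore neither headroom nor power.
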